	**Situation of the patient you are calling about:**
	• State name, department and room number of patient
	• Give a short overview of the problem and state when you visited the patient

**B**	**Background**
	**Relevant information about the background *can *include the following:**
	• Date of admission and admission diagnosis
	• Date of surgery, wound status and information about drains
	• Lab results and most recent vital signs. Is the patient using oxygen?
	• Medication overview, allergies, IV fluids
	• Other relevant clinical information
	• Mental status of the patient (delirium?)
	• Code status

**A**	**Assessment**
	**What is your assessment of the situation of the patient?**

**R**	**Recommendation**
	**What is your recommendation for this situation, examples:**
	• Come and see the patient as soon as possible
	• What actions should be taken when the situation changes?

	**Write down the comment of the physician in the patient record and changes in the condition of the patient.**

##### Evaluation

The first step is to determine to what extend and under what circumstances the SBAR tool is used by the nurses. We consider the implementation successful when 60% of the nurses uses the SBAR structure during communication moments. The use and possible effectiveness of the SBAR will be evaluated with different methods. First, short interviews will be conducted with some of the nurses of the intervention wards to discuss the possible added value, reasons for using or not using the instrument and possible improvements in the instrument or implementation for the future. Second, during the research period, observations of the morning rounds will be conducted on a regular base, approximately once a month. During these observations the process and content of communication and information transfer between nurse and physician during the morning rounds will be observed. Also, for each individual patient, it will be observed whether the different relevant topics of the SBAR-communication tool are discussed or mentioned. These aspects are, when applicable: current situation of the patient, special circumstances, possible risks, required actions, timing of the actions, reporting back, and finally, is the structure of the SBAR being used. The third evaluation moment is during the retrospective patient record review of the included patients. Here, the completeness and transfer of information in the patient record will be reviewed.

#### Intervention B: Involving patients and their families (Research question 2b)

##### Aim

To involve patients more actively in their own care process.

##### Background

The second intervention consists of a card with advice for patients about how to get more actively involved in the care process. The card was developed by the Federation of Patients and Consumer Organisations in the Netherlands (NPCF). This patient safety card provides patients with short instructions and graphical images for several topics to discuss with care providers that might be relevant for the safety of their care process. These instructions are in short:

• Give all information to the care providers about your state of health;

• Ask the care provider when something is not clear to you;

• Discuss the surgical procedure with the care provider;

• Write down an overview of your medication use;

• Ask questions when your medication looks different from expected;

• Follow the instructions given by your care provider.

##### Implementation

Within the research programme, half of the included patients in the intervention wards will receive the patient safety card. The card will be given to the patients during the hospital admission with a short instruction on how to use the card.

##### Evaluation

The implementation and effectiveness of the patient safety card will be established during an interview by telephone with the patient two weeks after discharge. We will consider the patient safety card successful when 60% of the patients has used the card and found it useful. One of the topics in the interview is therefore about the use and possible added value of the patient safety card and the need and possibility for patients and their family to get actively involved. Also, the possible consequences of the use of the patient safety card on the patients' trust in health care are discussed during these interviews. Finally, during the retrospective patient record review six months after discharge the number of complications and adverse events will be determined and compared to the baseline measurement.

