### Aim and research questions

The aim of this randomised controlled trial (RCT) is to evaluate the effectiveness of a patient safety intervention programme for elderly hip fracture patients. Therefore, the following research questions will be addressed:

1. What is the nature and scale of adverse events and avoidable harm in the care chain for elderly hip fracture patients?

2. How is it, in the total care chain of elderly hip fracture patients, possible to reduce risks and unintended harm, and to ensure that complex care processes proceed more safely? This research question is divided into sub-questions for the three interventions:

a What is the effectiveness of the SBAR communication tool on unintended events and avoidable harm during hospital stay? (Intervention A)

b What is the effectiveness of a patient safety card with guidelines for patients and their families on signalling errors and patient trust in health care? (Intervention B)

c What is the effectiveness of evidence based bundles with regard to unintended events in the period after discharge? (Intervention C)

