### Blinding

In this trial blinding of the patients is not possible as they either do or do not receive the material belonging to the interventions, and are therefore automatically aware of the intervention group. Since the physicians will not be directly involved in the inclusion of patients they are unaware of the intervention group a patients belongs to. For the assessment of the outcomes during a telephone interview two weeks after discharge the interviewer will be aware of the intervention group a patient belongs to because specific additional questions for each intervention group will be asked to evaluate the interventions. However, the interviewer will not be informed about the background, research questions and outcome measures of this study. For the telephone interview six months after discharge the interviewer will be unaware of the intervention group that the patient belongs to. Finally, the reviewers in the retrospective record review study will be blinded, they will assess some of the outcome measures and should therefore be unaware of the interventions that a patient might or might not have received to prevent possible biases in their assessment.

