##### Evaluation

The use of the leaflet will be evaluated by asking the patient about the added value and the usability of the bundles during a short interview by telephone two weeks after discharge. We will consider the leaflet useful if 60% of the patients says they have used the leaflet and found it useful. The effect of the bundles will be evaluated during the telephone interview two weeks after discharge and by measuring avoidable harm (e.g. adverse medication events, urinary tract infections, wound infections, delirium, falls and pressure ulcers) within 6 months after discharge. The patient will be called again around 6 months after discharge to ask about any medical problems occurring after discharge and their recovery in the past six months. Also, the patient records of all included patients will be reviewed by experienced reviewers for additional information about possible complications and avoidable harm after discharge.

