### Outcome measures

The primary outcome measures in this study are the incidence of complications and adverse events, mortality rate within six months after discharge and functional mobility six months after discharge. Secondary outcome measures are length of hospital stay, quality and completeness of information transfer and patient satisfaction with the instruments.

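### Research question 2b asks whether the safety card affects error signalling and trust, but neither is a listed outcome and the stated evaluation does not use the randomised card versus no-card contrast

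*Protocol article*

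**What the plan says.** Under Aim and research questions, question 2b concerns the "effectiveness of a patient safety card with guidelines for patients and their families on signalling errors and patient trust in health care".

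Under Outcome measures, the primary outcomes are complications and adverse events, six-month mortality and six-month functional mobility. For the rest: "Secondary outcome measures are length of hospital stay, quality and completeness of information transfer and patient satisfaction with the instruments".

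The Evaluation text for Intervention B says "The implementation and effectiveness of the patient safety card will be established during an interview by telephone with the patient two weeks after discharge". It then gives three elements:

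- The card counts as successful if 60% of patients used it and found it useful.
- On trust, "the possible consequences of the use of the patient safety card on the patients' trust in health care are discussed during these interviews".
- Complications and adverse events from the six-month record review are set against the baseline measurement.

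General data collection and follow up states that all included patients are telephoned at two weeks and at six months. The common topics are residence, physical functioning, care use, unexpected events, and open questions on experiences.

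Under Blinding, the two-week interviewer knows the group "because specific additional questions for each intervention group will be asked to evaluate the interventions". The same section adds that this interviewer is not told the study's background, research questions or outcome measures.

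**The concern.** A research question about effectiveness needs an endpoint that matches it and a group to compare with. Question 2b names two endpoints, and the outcome list contains neither. The evaluation section promises to establish effectiveness but supplies a rule about acceptability, and that rule can be met whether or not the card changes trust or error signalling.

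At stake is a named research question. Followed as written, the trial could report the card as successful because recipients liked it, and have no planned randomised comparison on either of the two things it asked about. The design already contains that comparison and the telephone call at which the data could be collected.

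**Working it through.** **Step 1: match question 2b to the stated evaluation.**

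| Stated element | Concerns trust or error signalling? | Compares card with no card? |
|---|---|---|
| Primary outcomes (Outcome measures) | No | Not relevant to 2b |
| Secondary outcomes (Outcome measures) | No; the nearest is satisfaction with the instruments | Patients without a card cannot rate it |
| 60% used and found useful (Intervention B, Evaluation) | No | No, one group only |
| Discussion of consequences of card use for trust (same place) | Trust only | As worded, it presupposes having used the card |
| Complications and adverse events v baseline (same place) | No | No, before-after |
| Common interview topics (General data collection and follow up) | Neither is named; unexpected events come closest | All patients are asked, but not about the 2b endpoints |

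No row has both a 2b endpoint and the randomised contrast. Error signalling has no stated measure at all.

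**Step 2: the contrast that the design already holds.** Under Study design, groups 2 and 4 receive the card and groups 1 and 3 do not. All four groups have SBAR, and the leaflet is balanced across the two sides (groups 3 and 4). Under Power calculation, 80 patients are planned per group and 64 are required.

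- As planned: 2 × 80 = 160 v 160.
- After drop-out: 1 − 64/80 = 20%, so 2 × 64 = 128 v 128.

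**Step 3: the plan's own figure.** For a difference of 5% and SD 10% (a ratio of 0.5), two-sided alpha 0.05 and 80% power, n = 2 × (1.96 + 0.84)² / 0.5² = 62.7, so 63 per group. The t-test version gives 63.8, so 64, as stated. And 64/0.80 = 80. The figures reproduce, but they concern complications. They neither support nor weaken the present point. The protocol gives no sample-size reasoning for trust or error signalling.

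**Step 4: what the unused contrast could show.** Two-sided alpha 0.05, 80% power.

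If trust were a continuous score (an assumption; the protocol names no scale), the detectable difference is (1.96 + 0.84) × √(2/n) SD:

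- n = 160 per side: 2.80 × √(2/160) = 0.31 SD.
- n = 128 per side: 2.80 × √(2/128) = 0.35 SD.

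For a yes/no item, such as having raised a concern, the detectable difference d solves d = 1.96 × √(2p̄(1−p̄)/n) + 0.84 × √([p₁(1−p₁) + p₂(1−p₂)]/n), where d = p₂ − p₁ and p̄ is the mean of the two rates. The reference rates are assumptions, because the protocol gives none:

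| Rate without card | Detectable increase, 160 v 160 | Detectable increase, 128 v 128 |
|---|---|---|
| 50% | about 15 points | about 17 points |
| 70% | about 13 points | about 15 points |
| 80% | about 11 points | about 12 points |

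These calculations assume no card-by-leaflet interaction and no sharing of materials. Strengths and limitations accepts that room-mates may expose each other to the interventions. That would shrink the observed difference and lower the power for a given true effect.

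**The case against.** The strongest reply is that this is a condensed article. The full questionnaire may hold trust items for everyone, and questions on unexpected events and experiences overlap with errors noticed. The Intervention B interview also covers the wish and opportunity to be involved, which any patient could answer. Data analysis promises intention-to-treat analysis at patient and group level. This reply stands in part: missing item wording is no finding, and a reader who inferred that no comparable data would exist would go beyond the text. It does not rescue the parts that the article does state. The research question, outcome list, success rule and comparator are all given, and they do not fit together.

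A second reply concerns blinding. A reader might infer that 2b lacks a comparison because the two-week interviewer is unblinded, or that interviewer bias reaches the main results. Neither is supported. The gap comes from the outcome list and the card-specific evaluation. The protocol keeps that interviewer uninformed about the background, questions and outcomes, has records assessed by blinded reviewers, keeps the six-month interviewer unaware of group, and assigns no primary outcome to the two-week call. What remains exposed is the common two-week items and part of the leaflet evaluation ("The effect of the bundles will be evaluated during the telephone interview two weeks after discharge"). Nor would question order remove the exposure: patients know what they received and may mention it in open answers.

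Third, a reader might attack the 60% threshold because a true value of 60% would pass only about half the time. That is true of nearly any cut-off placed at the true value and shows no defect. The same percentage is used for SBAR explicitly as a mark of successful implementation, and it is reasonable in that role.

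**Conclusion.** The point holds as a mismatch within the protocol. Question 2b has two endpoints. Neither is a listed outcome, neither is a stated interview topic for all patients, and the evaluation that claims to establish effectiveness rests on one-group acceptability, a discussion of card use and trust, and a before-after comparison of other endpoints. The randomised contrast of about 160 v 160 (128 v 128 after 20% drop-out) is not used for 2b.

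Confidence in this textual conclusion is high. The 0.31 to 0.35 SD only illustrates what the contrast could offer. It depends on a continuous trust score, no interaction with the leaflet and no contamination between room-mates. The two-week interviewer's knowledge of group is a secondary weakness that the protocol partly mitigates. The listed primary outcomes are unaffected, so this should be corrected but does not undermine the trial as a whole.

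**What to change.** 1. Add the same short closed items to the two-week interview for every patient in every group: trust in care, and errors or concerns noticed and raised.
2. List these as the outcomes for question 2b, and state the comparison as groups 2+4 v groups 1+3 within the intervention wards. The control ward is not part of the randomisation, so its answers are descriptive for this question.
3. Keep the 60% figure as a measure of implementation and acceptability, and do not present it as evidence of effectiveness.
4. Order the form so that the common items are asked first, with the group hidden, and the group-specific sheet is opened only afterwards. This reduces the remaining risk of interviewer bias for 2b and for the leaflet.

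The cost is a few extra items and a re-ordered form. The calls to all included patients are already planned, and no extra patients are needed.

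### The only success criterion for the patient safety card is 60% self-reported use and usefulness, presented alongside effectiveness, with no comparator and no primary or question 2b outcome

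*Protocol article*

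**What the plan says.** All places are in the protocol article.

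- **Card (Intervention B, Evaluation).** The paragraph opens: "The implementation and effectiveness of the patient safety card will be established during an interview by telephone with the patient two weeks after discharge". The next sentence is the verdict rule: "We will consider the patient safety card successful when 60% of the patients has used the card and found it useful". Trust in health care is one topic of that interview. At the six-month record review, "the number of complications and adverse events will be determined and compared to the baseline measurement". No success criterion is attached to that comparison.
- **Question 2b (Aim and research questions).** "What is the effectiveness of a patient safety card with guidelines for patients and their families on signalling errors and patient trust in health care".
- **SBAR (Intervention A, Evaluation).** "We consider the implementation successful when 60% of the nurses uses the SBAR structure during communication moments". Here the 60% is limited to implementation.
- **Leaflet (Intervention C, Evaluation).** "We will consider the leaflet useful if 60% of the patients says they have used the leaflet and found it useful". A separate sentence covers effect: "The effect of the bundles will be evaluated during the telephone interview two weeks after discharge and by measuring avoidable harm".
- **Outcomes.** The section on outcomes states: "The primary outcome measures in this study are the incidence of complications and adverse events, mortality rate within six months after discharge and functional mobility". Mobility is assessed at the six-month point. Patient satisfaction with the instruments is a secondary outcome.
- **Study design.** Within the intervention wards patients are randomised to SBAR alone (group 1), SBAR and card (2), SBAR and leaflet (3), or all three (4).

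**The concern.** The card paragraph joins implementation and effectiveness in one sentence and then defines success by what recipients say about use and usefulness. A card that patients read and liked would pass even if complications, adverse events, signalled errors and trust were unchanged or worse. A card that 58% used and liked would fail even if complications fell.

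The one clinical check in the paragraph is a before-after comparison with the 2007 records. The design contains a randomised card v no-card comparison, but the card's evaluation does not name it. At stake is whether the trial's published verdict on the card answers question 2b or bears on the primary outcomes.

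**Working it through.** **1. What enters the card rule.** Written out: successful if (number who used the card and found it useful) / (number who received it) ≥ 0.60. The text says only 'patients'; recipients are the natural denominator, since nobody else can have used the card.

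| Quantity | Enters the rule? |
|---|---|
| Self-reported use and usefulness | Yes |
| Patients randomised to no card | No |
| Complications, adverse events, mortality, mobility (primary) | No |
| Signalled errors, trust (question 2b) | No |

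**2. Number of recipients.** The 60% has no stated derivation, so the only plan figure to reproduce is the group size (Power calculation). With a difference of 5, SD 10, two-sided alpha 0.05 and power 80%, n = 2 × (1.96 + 0.84)² × (10/5)² ≈ 63 by the normal approximation. The t-test gives 63.8, so 64, as stated. The planned 80 equals 64/0.80, which implies 20% drop-out. Card recipients are groups 2 and 4: 2 × 80 = 160 as included, or 2 × 64 = 128 after that drop-out.

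**3. How often the rule is met.** P(X ≥ 0.60n) with X binomial. The true rate is an assumption, because the protocol gives none.

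| True 'used and useful' rate | n = 160 (at least 96) | n = 128 (at least 77) |
|---|---|---|
| 50% | 0.007 | 0.013 |
| 55% | 0.116 | 0.139 |
| 60% | 0.534 | 0.524 |
| 65% | 0.920 | 0.892 |
| 70% | 0.997 | 0.993 |

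No clinical outcome is an input, so as a test of clinical effect the rule carries no information. An observed 96/160 = 60% has a Wilson 95% interval of 52% to 67%.

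**4. What the baseline comparison can show.** Let b be the 2007 complication risk, t any change due to calendar time or case mix, and s, c and l the effects of SBAR, card and leaflet, taken as additive for illustration.

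- Group 2 minus baseline = t + s + c.
- Group 4 minus baseline = t + s + c + l.
- Mean of groups 2 and 4 = b + t + s + c + l/2. Mean of groups 1 and 3 = b + t + s + l/2. Difference = c.

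The baseline comparison never isolates c, because every patient on the intervention wards is exposed to SBAR (Randomisation). There is also reason to expect t ≠ 0. The baseline review excludes pathological fracture, polytrauma and elective admission (Baseline measurement, Method). The trial additionally requires good cognitive condition (Participants). The randomised contrast removes t and s; if card and leaflet interact, it estimates the card effect averaged over leaflet and no leaflet.

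**5. Leaflet.** By the same algebra, groups 3+4 minus groups 1+2 gives l. The leaflet text already keeps use apart from effect, but does not say which comparison the avoidable-harm data will serve.

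**The case against.** The best defence is that the 60% figure is an uptake benchmark. All three interventions carry one, and the SBAR version says so outright. In the card paragraph the sentence after the threshold ties it to use and possible added value, and complications follow under a separate 'finally'. Trial-level effect is handled elsewhere: the primary outcomes are listed, the power calculation concerns complications, and analysis is by intention to treat. Nothing there refers to 60%. A descriptive benchmark also needs no error control.

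Much of this stands, and it rules out several stronger readings that a reader might infer:

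- *That the leaflet too can be declared successful without effect.* Its rule yields 'useful', and its effect is evaluated separately through avoidable harm.
- *That the card rule ignores every outcome.* Satisfaction with the instruments is a listed secondary outcome close to 'found it useful'.
- *That clinical outcomes are not examined.* They are planned for both materials. What is missing is a link from them to the card's verdict.
- *That the binomial figures are false-positive rates.* They describe how a 60% threshold behaves. Their independence from clinical effect follows from the rule's form and is not an empirical result.

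The defence does not clear the card text. SBAR's rule is limited to implementation; the card's is not, and it follows directly on a sentence that places effectiveness in the same interview. The remaining clinical check uses the wrong comparator. The programme-level statements do not help either: General data collection and follow up assigns the second record review to the complete programme, and the power calculation's 5% reduction is also for the programme. This is stated text, not detail left to an analysis plan.

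**Conclusion.** The point holds for the card. Its only stated success criterion measures uptake and acceptability, sits under the heading of effectiveness, and can be met with no benefit, or with harm, on the primary and question 2b outcomes. If the true rate of 'used and useful' is 65%, the verdict is 'successful' about nine times in ten (0.92 with 160 recipients, 0.89 with 128) whatever the clinical effect. That rate is assumed; the conclusion that clinical effect plays no part needs no assumption.

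The before-after comparison cannot fill the gap, since SBAR and any change in period or case mix are mixed with the card. For the leaflet only the comparator is left open. The documents do not show that the trial's overall conclusion rests on 60%, and that should not be inferred. The point is worth correcting before analysis because it changes what can be concluded about the card, but it does not undermine the trial.

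**What to change.** **Card (Intervention B, Evaluation).**

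- Call the 60% threshold an implementation criterion (uptake and acceptability), in line with SBAR. Remove effectiveness from the sentence about the interview. Report the percentage with its 95% confidence interval over all patients allocated to the card.
- Replace the baseline comparison, as the basis for the card's effect, with the randomised contrast of groups 2+4 v 1+3 on complications, adverse events, mortality and mobility, with effect estimates and 95% confidence intervals.
- Apply the same contrast to trust and signalled errors only where these are asked of all groups. The Blinding section says that the two-week interview has group-specific questions, and the card paragraph frames trust as a consequence of using the card, so comparable data in non-recipients are not shown.

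**Leaflet (Intervention C, Evaluation).** Add one sentence: effect is judged by groups 3+4 v 1+2. The 60% rule for 'useful' can stay.

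**Cost.** Wording in two paragraphs, with no new data for outcomes collected in all included patients. Comparable trust or error-signalling data might need extra questions for non-recipients. Good uptake alone could no longer be reported as success.

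The contrast will be imprecise. With 160 v 160 and the same risk p in both arms, the 95% half-width is 1.96 × √(2p(1−p)/160): about 7 points at p = 10%, 10 at 30% and 11 at 50% (assumed risks). This is why the estimate and interval should be reported, not just a significance verdict.
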